### Participants

We aim to enroll 500 adult ICU patients over a period of 24 months. To identify eligible individuals, a daily screening of all critically care admissions will be performed by study investigators. Patients will be included in this study if they are expected to stay at least 48 h in the ICU, meet at least one of the following inclusion criteria, and have none of the exclusion criteria.

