### Randomization and blinding

Study patients will be randomly assigned to either LUS guided fluid management or usual care, in a 1:1 ratio, using block randomization. The randomized block design will be created using a computer-based program by a study team member not involved in patient enrollment and treatment. This team member will securely guard the randomized block design at the coordinating center and will provide the allocation sequence each time a new patient is enrolled. Due to study design, patients and ICU physicians cannot be blinded, but the researcher that investigates primary and secondary outcomes will be blinded to patient group assignment.

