### Primary outcome

The main outcome will be death from all causes at 28 days from randomization. This will be assessed by a study team researcher, blinded to patient group assignment, based on hospital recordings or a brief telephone interview with the patient or patients’ legally authorized representative or relative.

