### Statistical analysis

Statistical analysis will be performed using SPSS (SPSS Inc., Chicago, IL, USA) and conducted on an intention-to-treat basis. Frequency distributions will be calculated for all variables and descriptive statistics will be used to define patient’s characteristics in both arms. Study groups will be compared using non-parametric and parametric statistics, according to the types of variables analyzed.

The relative risk of 28-day mortality, with 95% confidence interval, will be assessed in both trial arms. Based on identified mortality-associated variables, we will also perform sensitivity analyses, subgroups analyses, and interactions tests.

Secondary outcomes will be analyzed using univariate analysis and competing-risk methods.

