### Sample size power calculation

Based on sample size power calculations, for a targeted power of 80% and alpha value of 0.05, the number of patients needed to reveal a significant decrease of 10% in mortality is about 500 (250 in each arm). The mortality benefit estimation is based on a large cohort study of ICU patients, which showed that without any specific intervention, the presence/absence of fluid overload resulted in a mortality rate of 20% and 16.8%, respectively [4].

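### The 250 per arm cannot be reproduced from the rates given as its basis, and has about 15% power, not 80%, for the cited 20% versus 16.8%

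*Protocol article*

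**What the plan says.** The protocol article, under Sample size power calculation, sets its targets ("for a targeted power of 80% and alpha value of 0.05") and its result: "the number of patients needed to reveal a significant decrease of 10% in mortality is about 500 (250 in each arm"). The next sentence names the source of the effect: "The mortality benefit estimation is based on a large cohort study of ICU patients". In that cohort, without any specific intervention, "the presence/absence of fluid overload resulted in a mortality rate of 20% and 16.8%, respectively".

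The section does not say what control-arm mortality was used, whether the 10% is absolute or relative, whether the test is one- or two-sided, or whether attrition was allowed for.

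The rest of the design fits a comparison of two proportions. Allocation is "in a 1:1 ratio, using block randomization" (Randomization and blinding). The endpoint is binary: "The main outcome will be death from all causes at 28 days from randomization" (Primary outcome). The planned summary is a relative risk with its confidence interval (Statistical analysis). The Participants section repeats the total of 500.

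**The concern.** The section presents three things as one chain: a pair of mortality rates, a 10% benefit said to rest on them, and 250 per arm at 80% power. The first link fails on inspection, because 20% versus 16.8% is not a 10% difference on either scale. If the second link also fails, the 80% does not describe the trial under the rates offered to justify it.

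This is the only justification given for the size of the trial on its primary endpoint. A reader who accepts it would believe that the trial has a good chance of detecting a benefit of the size seen in the cohort. If the true benefit were that size, the trial would miss it about 85% of the time.

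**Working it through.** **Inputs.** Power 80%, alpha 0.05, 250 per arm, and the rates 20% and 16.8% come from Sample size power calculation. The 1:1 ratio comes from Randomization and blinding, and the binary endpoint from Primary outcome. Assumption: two-sided test, since sidedness is not stated; one-sided results are given as a check.

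**Formulas** (two proportions, normal approximation, no continuity correction). With d = p1 − p2, p̄ = (p1 + p2)/2, A = √[2p̄(1 − p̄)] and B = √[p1(1 − p1) + p2(1 − p2)]:

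- n per arm = [(1.960·A + 0.842·B)/d]²
- power = Φ[(d·√n − 1.960·A)/B]

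**Step 1: the cited pair on each scale.** Absolute: 20 − 16.8 = 3.2 points. Relative: 3.2/20 = 16%. Neither is 10%.

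**Step 2: trying to reproduce 250 from the stated rates.**

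| Reading | Rates | n per arm for 80% | Power at 250 per arm |
|---|---|---|---|
| Cited pair as arm rates | 20% vs 16.8% | 2,301 | 15% |
| 10 points down from 20% | 20% vs 10% | 199 | 88% |
| 10% relative from 20% | 20% vs 18% | 6,039 | 8% |
| 10 points down to 16.8% | 26.8% vs 16.8% | 267 | 77% |
| 10 points down from 16.8% | 16.8% vs 6.8% | 163 | 94% |

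First row in full: p̄ = 0.184, A = 0.5480, B = 0.5475.

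- n = (1.5348/0.032)² ≈ 2,300.5, so 2,301 per arm or about 4,602 in total.
- Power at 250 = Φ[(0.032 × 15.811 − 1.960 × 0.5480)/0.5475] = Φ(−1.04) = 0.150. Counting rejections in the wrong direction as well gives 0.152.

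No row gives 250.

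**Step 3: other test conventions.** One-sided, 20% vs 16.8% needs 1,812 per arm (power 24% at 250) and 20% vs 10% needs 157. With continuity correction, two-sided, these become 2,363 and 219. None is 250.

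**Step 4: what does give about 250.** Each route adds something the section does not state.

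- 25% vs 15%, two-sided: A = 0.5657, B = 0.5612, n = (1.5811/0.10)² = 249.98, power 80.0%. Two-sided control rates of about 24% to 26% with a 10-point fall come close enough.
- 23% vs 13%, two-sided with continuity correction: 251.
- 30% vs 20%, one-sided with continuity correction: 251.
- 20% vs 10% with 20% attrition: 199/0.8 = 249.

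**Step 5: what 250 per arm delivers from 20%.** Power reaches 80% at an active rate of 10.95%. That is a fall of 9.05 points and a relative risk of 0.1095/0.20 ≈ 0.55. It is also 9.05/3.2 ≈ 2.8 times the cited difference. From 25%, the corresponding fall is 10 points, a relative risk of 0.15/0.25 = 0.60.

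**The case against.** The strongest reply is that a correct calculation may lie behind the 250. The text says about 500, and a condensed article may leave inputs to a fuller document. One route starts from a control rate that the section does cite: 20% falling to 10% needs 199 per arm, and a 20% attrition allowance brings that to 249. On that reading 250 per arm is ample for the 10-point target, with 88% power before any loss.

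Part of this stands. A reader might infer that the sponsor's calculation was done wrongly. The document does not show that, because several sets of unreported inputs lead to about 250. For the same reason, 25% to 15% is a back-calculation and should not be treated as the assumption the sponsor made.

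The reply does not save the justification as printed. Every route needs an input the section omits, and every one assumes a 10-point fall, about three times the cited difference. An unseen document could supply a control rate or an attrition allowance, but it could not turn 3.2 points into 10. Nor can the cohort be set aside as background, because the text says the benefit estimate rests on it.

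A reader might also infer that a non-significant result will be reported as absence of benefit. Nothing in the document says so, and the Statistical analysis section already commits to an interval: "The relative risk of 28-day mortality, with 95% confidence interval, will be assessed in both trial arms".

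**Conclusion.** The concern holds in this form: the sample size is neither reproducible from nor supported by the figures stated for it. For the cited pair, power at 250 per arm is about 15% against the stated 80%, and about 2,300 per arm would be needed. This rests on a two-sided 5% test without continuity correction and on taking the two cited rates as arm rates. A one-sided test raises the power only to 24%.

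The second assumption is probably generous. The cohort compares patients with and without overload, whereas each randomised arm will mix the two, so the difference between arms could be below 3.2 points and the power below 15%.

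The finding does not show that 500 is inadequate for every effect. The trial has 80% power for about a 9-point fall at 20% control mortality and for a 10-point fall at 25%. What fails is the link between the cited evidence and the claimed power. It needs correcting because it is the only basis given for N.

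**What to change.** Keep N = 500 and rewrite Sample size power calculation as follows.

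1. State the inputs actually used: control-arm 28-day mortality, the target effect labelled as absolute, sidedness, and any attrition allowance. The sponsor should supply these from its own records and not adopt 25% to 15% because it returns 250.
2. Stop presenting the 20%/16.8% cohort as the source of the 10% effect.
3. State what the design delivers, for example: with 250 per arm and a two-sided 5% test, power is 80% for a fall of about 9 points at 20% control mortality (to about 11%, relative risk about 0.55) or 10 points at 25% (to 15%, relative risk 0.60), and about 15% for 20% versus 16.8%.

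The cost is wording in one section, with no extra patients and no change to the analysis. The stated power becomes less favourable. The change discloses the limitation and does not remove it: power for the cited difference stays at about 15%.

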### Strengths and limitations of the study protocol

To our knowledge, this is the first prospective randomized controlled study that aims to evaluate a fluid management protocol for adult ICU patients, based on the daily assessment of BLS compared to usual care. A pre-specified BLS cut-off value of 15 will be used to assess fluid overload.

Our study will address both surgical and medical ICU patients. To identify eligible patients, we use severity scoring systems, but inclusion criteria are not limited to them, as scoring systems alone may be poor determinants of the level of care. ICU patients at risk for postsurgical organ dysfunction due to surgery magnitude or co-morbidities are also included.

LUS data may depend on examiner, ultrasound system, and patients’ particularities. In order to minimize bias, LUS will be performed by previously trained investigators, using the same type of ultrasound equipment, probe, and technique. Patients with pulmonary conditions known to interfere with BLS evaluation (pneumectomy, pulmonary fibrosis, persistent pleural effusion) will be excluded, but other conditions, such as obesity, extrapulmonary diseases in the examination area, cardiac assist devices, or wound dressing, may also render the LUS examination difficult. To monitor LUS efficiency, B-lines will be counted in every site of examination and inaccessible sites for B-lines visualization will be noted. Although we cannot exclude all bias, the before mentioned strategies aim to minimize potential errors.

Diuretic prescription in overhydrated hemodynamically unstable patients may result in decreased protocol adherence. Therefore, protocol deviations (e.g. deviation from diuretic regimen) will be recorded and analyzed.

Due to the study design, the ICU physician in charge is not blinded to each patient’s group allocation. Investigators in charge with biomarkers measurement and outcome assessment will be blinded. This may influence fluids and diuretics prescription, which may further modify the incidence of fluid overload and alter the results.

## Discussion

The attempt to improve fluid management in critically ill patients has led in the last few years to a refined approach, centred on volemic status and fluid responsiveness assessment. Many studies have addressed the hemodynamically unstable patient and assessed different methods used to predict fluid responsiveness [49]. Less attention has been given to the diagnosis and management of fluid overload, mainly in patients at risk for organ dysfunction. Our study protocol includes patients at risk (patients after major surgery, surgical patients with major co-morbidities) and concentrates on active measures to detect and correct fluid overload.

Dynamic measurements of cardiac output and related parameters, although proven to be superior to static methods in directing fluid therapy [49], are still marginally used in clinical practice [50]. Offering fast results, being safe, non-invasive, and easy to learn [39, 51, 52], LUS has the potential to overcome the drawbacks of other fluid assessments methods. If our study hypothesis proves to be right, LUS and BLS may help to discriminate between patients that may benefit from further fluid repletion and patients in which a fluid evacuation strategy should be adopted. LUS is not supposed to replace invasive hemodynamic monitoring or other methods used to assess fluid responsiveness, but to help intensive care physicians by providing a safety threshold for fluid resuscitation. More than this, for patients with pulmonary congestion, an algorithm for fluid management is proposed, with specific therapeutic measures that should be taken in order to achieve specific endpoints.

Study results will be submitted to an ISI indexed scientific journal. Other dissemination methods will include presentations at national and international scientific meetings. Favourable results may also be the ground for further research aiming for fluid management protocols based on non-invasive, simple, reliable, bedside techniques.

## Trial status

Patient enrollment in the trial started in November 2017 and is expected to end in October 2019. The trial is registered at ClinicalTrials.gov, NCT03393065. Registered on 8 January 2018 – retrospectively registered. Protocol version: 1.

## Abbreviations

AKI: Acute kidney injury
APACHE II: Acute Physiology and Chronic Health Evaluation II Score
BLS: B-lines score
EVLW: Extravascular lung water
ICU: Intensive Care Unit
IL-6: Interleukin-6
ISS: Injury Severity Score
LUS: Lung ultrasound
NGAL: Neutrophil gelatinase-associated lipocalin
NT-proBNP: Brain natriuretic peptide
RRT: Renal replacement therapy
SOFA: Sequential Organ Failure Assessment Score
